## Abstract

**Background:**

The increase in the number of people with dementia will lead to greater demand for residential care. Currently, large nursing homes are trying to transform their traditional care for residents with dementia to a more home-like approach, by developing small-scale living facilities. It is often assumed that small-scale living will improve the quality of life of residents with dementia. However, little scientific evidence is currently available to test this. The following research question is addressed in this study: Which (combination of) changes in elements affects (different dimensions of) the quality of life of elderly residents with dementia in long-term care settings over the course of one year?

**Methods/design:**

A longitudinal comparative study in traditional and small-scale long-term care settings, which follows a quasi-experimental design, will be carried out in Belgium and the Netherlands. To answer the research question, a model has been developed which incorporates relevant elements influencing quality of life in long-term care settings. Validated instruments will be used to evaluate the role of these elements, divided into environmental characteristics (country, type of ward, group size and nursing staff); basic personal characteristics (age, sex, cognitive decline, weight and activities of daily living); behavioural characteristics (behavioural problems and depression); behavioural interventions (use of restraints and use of psychotropic medication); and social interaction (social engagement and visiting frequency of relatives). The main outcome measure for residents in the model is quality of life. Data are collected at baseline, after six and twelve months, from residents living in either small-scale or traditional care settings.

**Discussion:**

The results of this study will provide an insight into the determinants of quality of life for people with dementia living in traditional and small-scale long-term care settings in Belgium and the Netherlands. Possible relevant strengths and weaknesses of the study are discussed in this article.

**Trial registration:**

ISRCTN: ISRCTN23772945

## Background

The substantial increase in the number of people with dementia worldwide implies that there will be much greater demand for both home care and residential care in the future [1]. For the Netherlands, the expectation is that in 2030 there will be 319,312 people with dementia, an increase of 65% over a period of 25 years [2]. The expectation for Belgium is that there will be 251,000 people aged over 65 with dementia in 2030, a rise of 56% over 25 years [3].

People usually prefer home care over residential care, but for a substantial number of people in the later stages of dementia staying at home is no longer possible [4]. In the last decade, the institutional regime in traditional, large nursing homes with a strongly medical and nursing-based approach, the hospital-like environment and the lack of privacy, has come in for heavy criticism in many countries [5-8]. To address this criticism, many large nursing home organizations are currently transforming their traditional care methods to a more home-like approach by developing small-scale living facilities [9-11]. The number of these small-scale living facilities has been increasing in many countries all over the world, such as Sweden, the United States, Germany, Belgium and the Netherlands. They take a variety of forms and the expansion is taking place at different rates in each country [5,12,13].

The assumption that small-scale living facilities will improve the quality of life of older persons with dementia compared to traditional nursing home care is often made by organizations that provide care for the elderly [8,14-16], as well as by politicians and other policymakers [17-20]. However, little scientific evidence is currently available about the effects of small-scale living on the quality of life of these residents [5,21]. Quality of life is defined by the World Health Organization (WHO) as "individuals' perceptions of their position in life in the context of the culture and value systems in which they live and in relation to their goals, expectations, standards and concerns" [22]. The physical, psychological, social and environmental domains are considered to be the most important indicators of quality of life [22,23].

The aim of this study is to contribute to the knowledge about the effects of small-scale living on the quality of life of residents with dementia by answering the following main research question: Which (combination of) changes in elements affects (different dimensions of) the quality of life of elderly residents with dementia in long-term care settings over the course of one year?

The relevant elements taken into account in this study are country (the Netherlands or Belgium), type of ward (traditional or small-scale), group size, nursing staff, age, sex, cognitive decline, weight, activities of daily living (ADL), behavioural problems, depression, use of restraints, use of psychotropic medication, social engagement and visiting frequency of relatives.

## Methods

This study is a longitudinal comparative study of elderly residents with dementia in long-term care settings in Belgium and the Netherlands.

### Sample size considerations

Sample size calculations are conducted for two groups (small-scale and traditional living) based on the primary outcome measure for residents, quality of life, as measured by the QUALIDEM [24]. Using an effect size of 0.50, a two-sided significance level α of 0.05 and a power of 80%, about 70 participants are needed in each group. Expecting an average drop-out rate of 20%, we aim to include about 180 residents. From the five long-term care settings that were selected for this study, 179 residents can be included.

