### Small-scale living facilities and traditional care wards

Small-scale living facilities and traditional institutional psychogeriatric wards will be compared, based on the numerous differences between these two types of settings and the assumption that there will be a concomitant difference in the quality of life of the residents. Five long-term care settings have been selected for the study, of which two have traditional care wards and four have small-scale living wards: one of the settings has both small-scale and traditional wards. The long-term care settings were selected in advance, taking into account the comparability of the frailty of the residents. All residents willing to participate will be included in this study. An overview of the settings can be found in Table 1.

**Table 1 T1:** Wards

Country	Long-term care setting	Small-scale wards N	Traditional wards N	Total at T0 N
*The Netherlands*	*A*	13	51	64

	*B*	24		24

	*C*	14		14

*Belgium*	*D*	47		47

	*E*		30	30

**Total N**		**98**	**81**	**179**

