### Environmental characteristics

The relevance of country and type of ward for quality of life has already been discussed. Group size is an important factor from the micro-environment, because wards can vary in the number of residents (between six and 27), and nursing staff is an important factor, because staffing levels and education level can differ. At T0 country (the Netherlands or Belgium), type of ward (small-scale or traditional), group size (between six and 27) and nursing staff (staffing levels of qualified nurses and of other assistant staff) are recorded.

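### The stated 80% power holds only if residents are independent or the within-ward correlation is very small, and the protocol should say so and give a range

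*Protocol article*

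**What the plan says.** Under Sample size considerations, the article gives a complete calculation. It compares two groups ("Sample size calculations are conducted for two groups (small-scale and traditional living") on the QUALIDEM. The inputs are "Using an effect size of 0.50, a two-sided significance level α of 0.05", and the result is "a power of 80%, about 70 participants are needed in each group". Drop-out is then added: "Expecting an average drop-out rate of 20%, we aim to include about 180 residents". Availability sets the limit: "From the five long-term care settings that were selected for this study, 179 residents can be included". No ICC, design effect or cluster size appears in this calculation.

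Other sections describe a clustered design:

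- The section on small-scale facilities and traditional wards states: "Five long-term care settings have been selected for the study, of which two have traditional care wards and four have small-scale living wards". One setting has both types. Table 1 lists 98 small-scale and 81 traditional residents. Setting A has 13 and 51; B, C and D are small-scale only (24, 14 and 47); E is traditional only (30).
- Conceptual model places type of ward in the micro-environment, together with group size and nursing staff.
- Environmental characteristics says that "wards can vary in the number of residents (between six and 27").
- Quality of life says that two caregivers who know the resident complete the QUALIDEM together.

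Analyses states the null hypothesis as equal patterns of change over time on the QUALIDEM subscales in the two types of setting.

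**The concern.** Ward type does not vary within a ward. Residents of one ward share staff, group and building, and probably the caregivers who rate their quality of life. Their scores are therefore likely to be correlated. For a ward-level exposure, positive correlation raises the variance of the group comparison by a factor that grows with the number of participants per ward. A calculation for independent persons then overstates the power.

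Two things are at stake. The first is whether 179 residents can be expected to show a difference of half a standard deviation, as the article implies. The second is how the small-scale versus traditional contrast is tested. A resident-level test that ignored the clustering would have standard errors that are too small. It could present a difference between a few buildings as an effect of small-scale living.

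**Working it through.** **Inputs from the article.** d = 0.50; two-sided α = 0.05; power 80%; about 70 per group; 20% drop-out; wards of 6 to 27 residents; Table 1 counts.

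**Assumed, because the documents do not give them.** ICC of 0.01, 0.02, 0.05 and 0.10. The number of participants per ward, m, is set to 6 and 27, the two ends of the stated ward-size range. The number of wards and the participants per ward are not stated.

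**Step 1: reproduce the stated figure.** Normal approximation: n = 2(1.96 + 0.84)²/0.50² ≈ 62.8, so 63 per group. The two-sample t-test needs 63.8, so 64. At 70 per group the t-test has 83.6% power. The drop-out step is sound: 140/0.8 = 175, close to 180. So about 70 is the figure for independent persons, rounded up.

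**Step 2: what the rounding covers.** 70/63.8 = 1.10. With design effect DE = 1 + (m − 1)ICC, 80% is kept while ICC ≤ 0.10/(m − 1):

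- m = 6: 0.10/5 ≈ 0.02
- m = 27: 0.10/26 ≈ 0.004

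**Step 3: power at 70 per group.** Effective n = 70/DE, entered in the two-sample t-test with d = 0.5.

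| ICC | DE, m = 6 | Effective n | Power | DE, m = 27 | Effective n | Power |
|---|---|---|---|---|---|---|
| 0.01 | 1.05 | 66.7 | 82% | 1.26 | 55.6 | 74% |
| 0.02 | 1.10 | 63.6 | 80% | 1.52 | 46.1 | 66% |
| 0.05 | 1.25 | 56.0 | 75% | 2.30 | 30.4 | 48% |
| 0.10 | 1.50 | 46.7 | 67% | 3.60 | 19.4 | 33% |

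If small-scale wards had 6 participants and traditional wards 27, the effective n would be 140/(DE₆ + DE₂₇), for example 140/(1.25 + 2.30) = 39.4 at ICC 0.05. Power over the four ICC values would be about 78%, 73%, 59% and 44%.

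These figures use resident-level degrees of freedom. With few wards the proper degrees of freedom are fewer and power is lower still, but the article does not give the number of wards.

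**Step 4: the same result as a detectable effect.** At 80% power, d ≈ 2.80 × √(2 × DE/70). This is 0.47 under independence. At ICC 0.05 it is 2.80 × √(2.5/70) = 0.53 for m = 6 and 2.80 × √(4.6/70) = 0.72 for m = 27.

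**Step 5: setting as a stratum.** Only setting A has both ward types, so a contrast within settings would rest on 13 versus 51 residents. At d = 0.5 that has about 35% power even with independent residents and no drop-out. In Belgium, small-scale means D and traditional means E, so ward type and setting coincide.

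**The case against.** **The ICC is unknown, so a shortfall is not shown.** This stands in part. At ICC 0.01 the power is 82% with 6 per ward and 80.3% with 10 per ward. A reader might infer that the study cannot reach 80%; the documents do not support that. They support a conditional statement: 80% needs independence or a very small ICC.

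**The hypothesis concerns change, not a single-time mean.** This also stands as a limit on the size of the loss. Stable differences between wards or raters cancel from change, so the relevant ICC may differ, and repeated measures can add precision. The printed calculation uses neither feature, so neither supports the 80%.

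**The article leaves the covariance model to a fuller document.** Agreed: silence on the model is no finding. A reader might infer that the planned test has a particular inflated error rate. The article specifies no pooled, unadjusted resident-level test, and it says that the analyses will be controlled for group size, nursing staff and other differences. Only the direction can be stated: a test that ignored clustering would reject too often. Adjustment for measured covariates need not remove the residual correlation within wards. The power statement is a different matter, because the article prints both its inputs and its result.

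**The arithmetic is not wrong.** Correct. The inputs give 64, and 70 errs on the safe side. The fault is an unstated independence assumption.

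**The sample is capped by availability.** True, and no increase is asked for.

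**Conclusion.** The point holds in conditional form. The printed 80% is the power for independent residents, with a margin equal to a design effect of about 1.10. That margin is used up at an ICC of about 0.02 with 6 participants per ward and about 0.004 with 27. Over assumed ICCs of 0.01 to 0.10, power runs from 82% down to 67% at the small end of the ward-size range, and from 74% down to 33% at the large end.

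This rests on three assumptions: the ICC range, which has no source in the documents; the ends of the stated ward-size range used as the number of participants per ward; and a single-time comparison of means. The direction does not depend on the chosen values, since any positive ICC for the tested contrast lowers the power below the independent-persons figure. The amount does depend on them. Separately, the Belgian comparison of ward types is a comparison of one setting with another, which no allowance for clustering can resolve.

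**What to change.** 1. In Sample size considerations, keep the 179 residents and state that 80% power is conditional on independent residents.
2. Restate the power, or the detectable effect, with DE = 1 + (m − 1)ICC for the actual numbers of participants per ward, over a stated ICC range. Say whether the ICC refers to a single-time score or to change.
3. State that the small-scale versus traditional contrast is tested with standard errors that allow for ward clustering, for example a random ward effect with a small-sample degrees-of-freedom correction such as Kenward-Roger.
4. Do not use setting as a stratum for this contrast, because only setting A would then contribute.
5. State that in Belgium ward type cannot be separated from setting (D versus E).

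The cost is some wording, a short recalculation and a few lines of SAS, with no additional residents. The stated power falls and the intervals widen. Item 5 is a limit on interpretation that the analysis cannot remove.

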### Small-scale living facilities and traditional care wards

Small-scale living facilities and traditional institutional psychogeriatric wards will be compared, based on the numerous differences between these two types of settings and the assumption that there will be a concomitant difference in the quality of life of the residents. Five long-term care settings have been selected for the study, of which two have traditional care wards and four have small-scale living wards: one of the settings has both small-scale and traditional wards. The long-term care settings were selected in advance, taking into account the comparability of the frailty of the residents. All residents willing to participate will be included in this study. An overview of the settings can be found in Table 1.

**Table 1 T1:** Wards

Country	Long-term care setting	Small-scale wards N	Traditional wards N	Total at T0 N
*The Netherlands*	*A*	13	51	64

	*B*	24		24

	*C*	14		14

*Belgium*	*D*	47		47

	*E*		30	30

**Total N**		**98**	**81**	**179**

### Belgium and the Netherlands

The choice of these two countries was primarily based on the existing collaboration between Tilburg University (the Netherlands) and K.U. Leuven (Belgium). The use of data from two different countries affords the possibility of comparison and the opportunity to learn from each other. There are also advantages as regards data collection, in that the two countries are geographically adjacent and the spoken language in both countries is Dutch. However, there are also differences, for example in legislation and the funding of long-term care, the design and number of small-scale living facilities (more facilities in the Netherlands), the group size (groups are generally smaller in the Netherlands) and the speed of development (a more rapid expansion of small-scale living can be observed in the Netherlands) [8,25].

### Study population

The study will include elderly residents over 65 years of age, with dementia and who have been admitted to a long-term care setting.

Dementia is a complex syndrome, which manifests itself in various forms and is characterized by an initially gradual and progressively deteriorating impairment of the brain functions [26]. The DSM-IV employs the presence of multiple cognitive impediments with disorders in memory functions as a criterion for diagnosing the disease [27]. The memory disorders appear in varying combinations with changes in personality, mood and behaviour [26]. Residents with dementia are often legally incapable, and the law therefore stipulates that a legal representative be appointed to look after their interests. For this study, these representatives will be asked to give informed consent on behalf of the residents [28-30].

Owing to the cognitive decline, self-reporting is often no longer possible for people with dementia. Observation by one or more professional caregivers is therefore considered to be the best, most reliable and valid alternative method of data gathering [31]. Questionnaire sets validated for the target group have been selected for the study, which can be completed by a professional caregiver, namely a nurse or nursing assistant, who is familiar with the resident. One of the questionnaires is filled in by an independent psychologist interviewing the nurse or nursing assistant who is familiar with the resident, and one will be used to gather information from the residents themselves.

### Ethical approval and informed consent

The ethics committee at De Wever, Tilburg, gave its approval for the study in September 2008. The trial is registered as ISRCTN23772945. In practice, we will consider our ethical responsibility to be to the residents and family that we wish to include in our study. There will be virtually no inconvenience to the residents, because professional caregivers will fill in the questionnaires for them. The legal representatives of the residents will receive an information brochure containing information on all aspects of the research. An informed consent form will accompany the brochure, for the representative to sign and return. Only residents for whom such consent has been given will be included in the study. All those involved will be informed that they may end their participation in the study at any time. The privacy of the participating residents will be protected and all data will be analyzed anonymously.

### Conceptual model

The following conceptual model (see Figure 1) will be used to answer the research question. The model was developed after studying the most relevant factors affecting the quality of life of persons with dementia as reported in the literature [7,32-51]. The main outcome in this model is the quality of life of elderly residents with dementia in long-term care settings. The model shows two categories of influence on quality of life. The first category describes the environmental characteristics, divided into macro-environment (country) and micro-environment (type of ward, group size and nursing staff). The second category describes basic personal and behavioural characteristics, behavioural interventions and social interaction. We assume that the environmental characteristics influence quality of life both directly and indirectly through the personal, behavioural and social aspects. The elements of the conceptual model will be measured using valid and reliable instruments. All scales (except for the recording of country, type of setting, age, sex and staff formation) will be measured at three moments over the course of one year: T0 (baseline), T1 (after six months) and T2 (after 12 months). An overview of the measurements and records can be found in Table 2. Most of the scales and record forms will be filled in by a nurse or nursing assistant who is familiar with the resident. One of the scales is administered by interviewing a nurse or nursing assistant, and one will be used for gathering information from the resident by an independent psychologist. All characteristics, their relation to quality of life and the proposed instruments to be used in the study are discussed below.

**Figure 1 F1:**
[figure not shown]
**Conceptual Model**.

**Table 2 T2:** Measurements and records

	Measurement moment		
	**T0 (start)**	**T1 (6 months)**	**T2 (12 months)**

**Quality of life (QUALIDEM)**			

Positive self-image	X	X	X

Restless behaviour	X	X	X

Feeling at home	X	X	X

Caregiver relationship	X	X	X

Social relations	X	X	X

Social isolation	X	X	X

Negative affect	X	X	X

Positive affect	X	X	X

Having something to do	X	X	X

**Environmental characteristics**			

Country (The Netherlands or Belgium)	X		

Type of ward (traditional or small-scale)	X		

Group size	X		

Nursing staff	X		

**Basic personal characteristics**			

Demographic data			

- Age	X		

- Sex	X		

Cognitive decline (S-MMSE)	X	X	X

Weight (Dossier)	X	X	X

Activities of daily living (Barthel Index)	X	X	X

**Behavioural characteristics**			

Behavioural problems (NPI-NH)	X	X	X

Depression (CSDD)	X	X	X

**Behavioural interventions**			

Use of restraints (Dossier)	X	X	X

Use of psychotropic medication (Dossier)	X	X	X

**Social interaction**			

Social Engagement (RISE from RAI)	X	X	X

Visiting frequency of relatives (Questionnaire relatives)	X	X	X

### Quality of life

Quality of life is a broad concept. The WHO originally divided quality of life into six domains incorporating physical health, psychological state, level of independence, social relationships, personal beliefs and the relationships to features of the environment [23]. Empirical evidence from the WHO showed that a four-domain solution might fit the data better in both ill and well populations:

1. The physical domain (pain and discomfort; energy and fatigue; sleep and rest);

2. The psychological domain (positive affect; cognition, memory and concentration; self-image; appearance; negative affect);

3. Social relations domain (personal relationships; social support; sexual activity);

4. Environmental domain (safety; financial resources; availability and quality of health care; access to new information and skills; leisure time; mobility) [22,23].

Qualidem (Quality of life in dementia) is a measurement scale used to determine aspects of the quality of life of elderly residents with dementia [24]. Using this scale, it is possible to determine how residents deal with and experience their immediate environment and what kind of relationship the elderly resident has with care giving staff and other residents. This instrument was developed and validated [52] specifically for residents in long-term care settings, over the age of 65 years and suffering from mild to severe dementia. Two professional caregivers, a nurse or nursing assistant who are familiar with the resident, observe the elderly resident and complete the questionnaire together. In this way, the scale provides a quality of life profile of residents with dementia [53]. The questionnaire comprises 40 items that can be divided into nine subscales. The subscales need to be assessed individually and are not suitable for calculating a total score. The subscales are Caregiver relation, Positive affect, Negative affect, Restless behaviour, Positive self-image, Social relations, Social isolation, Feeling at home and Having something to do. For each item, an answer between '0 = never' and '3 = often' can be chosen. Administering the questionnaire generally takes around 15 minutes [24].

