**Figure 2 F2:**
[figure not shown]
**Comparisons**.

To make a comparison, the data will be analyzed using descriptive, quantitative and qualitative analyses. The quantitative analyses will include cross-sectional and longitudinal analyses using SAS 9.2.1^©^. The null hypothesis that 'the patterns of change in the mean response over time on the Qualidem subscales are the same in both types of long-term care settings' will be tested. The qualitative analyses will be carried out using Qualitative Comparative Analysis using TOSMANA^© ^[70]. One of the general advantages of QCA is that it combines the strength of qualitative research (within-case knowledge) with the strength of quantitative enquiry (cross-case comparison) [71]. The most conventional and intuitive type of QCA analysis will be employed for the analyses: crisp-set Qualitative Comparative Analysis (csQCA). In csQCA, a dichotomous data table will be built, based on within-case knowledge, and from this dichotomous data table a set of necessary and sufficient conditions leading to a certain outcome will be deduced [72].

This approach integrates key strengths of both qualitative (case-oriented) and quantitative (variable-oriented) methods and allows triangulation. It provides a double check to ensure that valid results are obtained despite the relatively small number of participants.

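### The sample size powers one QUALIDEM outcome, but the instrument has nine subscales and no total; with 70 per group, 5% familywise error and 80% power per subscale cannot both hold

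*Protocol article*

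**What the plan says.** Three parts of the protocol article bear on this point.

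- **Sample size considerations.** The calculation is "based on the primary outcome measure for residents, quality of life, as measured by the QUALIDEM". It compares two groups (small-scale and traditional). The inputs are one effect size ("Using an effect size of 0.50"), one error rate ("a two-sided significance level α of 0.05") and 80% power, with the result that "about 70 participants are needed in each group". Drop-out is then added: "Expecting an average drop-out rate of 20%, we aim to include about 180 residents". No subscale is named.
- **Quality of life.** QUALIDEM has 40 items in nine subscales. "The subscales need to be assessed individually and are not suitable for calculating a total score".
- **Analyses.** The null hypothesis is that "the patterns of change in the mean response over time on the Qualidem subscales are the same in both types of long-term care settings". No subscale is put first, no joint test is specified, and no division of alpha is given.

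**The concern.** The sample size section needs a single score to carry the 0.50, the 0.05 and the 80%. The description of the instrument rules that score out. A reader cannot tell whether the stated power applies to one subscale, to every subscale, to at least one of them, or to a joint test, and these are different quantities.

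The study sets out to test a widely held assumption that small-scale living improves quality of life. If the rule for a positive result stays open, a difference on some subscales and not on others has no agreed reading, and the stated error rate and power cannot be attached to the conclusion.

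**Working it through.** **Inputs.** Effect size d = 0.50, two-sided alpha 0.05, power 80%, 70 per group and 20% drop-out (Sample size considerations); nine subscales (Quality of life); 98 small-scale and 81 traditional residents (Table 1). The documents give no correlation between subscales, so a range is assumed. Residents are treated as independent and compared by a simple two-group test of means, as the sample size section appears to do.

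**1. The plan's own figure.** n per group = 2(z₀.₉₇₅ + z₀.₈₀)²/d² = 2(1.960 + 0.842)²/0.25 ≈ 62.8, so 63 (64 by t-test). The stated 70 is not reproduced, but it errs on the safe side. The drop-out step is close: 140/0.8 = 175, against about 180.

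**2. Power for one given subscale at 0.05.** With 70 per group, d√(n/2) = 0.5√35 = 2.958. Power = Φ(2.958 − 1.960) = Φ(0.998) = 84% (also 84% by t-test).

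**3. Familywise error if all nine are tested at 0.05.** With independent subscales it is 1 − 0.95⁹ = 37%. Simulation of nine equally correlated normal test statistics gives:

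| Assumed correlation | Chance of at least one false positive |
|---|---|
| 0 | 37% |
| 0.3 | 33% |
| 0.5 | 27% |
| 0.7 | 20% |
| 0.9 | 12% |

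**4. Power for one given subscale at the Bonferroni level.** 0.05/9 = 0.0056, with critical value about 2.773. Power = Φ(2.958 − 2.773) = Φ(0.185) = 57% (56% by t-test).

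**5. The same with the expected completers.** 98 × 0.8 ≈ 78 and 81 × 0.8 ≈ 65. At 0.05/9 the power is 58% (57% by t-test).

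**6. Size needed for 80% at that level.** 2(2.773 + 0.842)²/0.25 ≈ 104.5, so 105 per group (107 by t-test). By t-test that is 214 completers, and 214/0.8 = 267.5, so 268 residents. The article has 179.

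**7. A different quantity: at least one adjusted rejection.** If all nine subscales had an effect of 0.50, power for at least one rejection at 0.05/9 would be about 98%, 93% and 87% at correlations 0.3, 0.5 and 0.7. The article does not assume an effect on all nine.

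**The case against.** The strongest reply is that this is a condensed article. Adjustment for multiple tests is commonly left to an analysis plan, and that plan is not shown. The null is worded as one statement and could be read as a joint or profile test. The requirement to assess subscales individually describes scoring and need not be a testing plan. The research question is openly about different dimensions of quality of life, so a single lead subscale may suit it poorly.

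Much of this stands, and it limits what can be claimed. A reader might infer four stronger points, which the document does not support:

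- *That neither the 5% nor the 80% holds.* Each fails only under the opposite assumption. Without adjustment, power per subscale is 84%; with adjustment, the 5% is kept.
- *That every subscale will be tested at the full 0.05.* The article gives alpha only in the sample size section and nowhere says that the tests are unadjusted.
- *That there are 9 × 4 = 36 primary tests, with a false-positive chance of 1 − 0.95³⁶ = 84%.* Two of the four central comparisons are between countries within one ward type and do not test the ward-type null. The comparisons also share groups, so independence fails.
- *That 56% is the power of Holm's first step.* It is the power for one given subscale at 0.05/9. The first step concerns the smallest p-value, and its power is the chance of at least one rejection, which can be much higher (step 7).

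The reply does not remove the core. The choice of endpoint and the sample size built on it are in the article itself. An unseen plan could supply an adjustment, but the stated 80% would then not describe power for a given subscale at the adjusted level. Nor does the sample size section describe a calculation for a joint test.

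**Conclusion.** The point holds in this form: the sample size rests on a single QUALIDEM outcome that, by the article's own account, does not exist as a score. With 70 per group, a 5% familywise error and 80% power for a given subscale cannot both hold. Unadjusted, power is 84% and the familywise error is about 20% to 37% for correlations of 0.7 down to 0; it is still 12% at 0.9. At 0.05/9 the familywise error is kept and power for a given subscale is about 56%, or about 57% with the expected completers.

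This rests on an effect of 0.50 on the subscale in question, assumed correlations, independent residents, and no assumed effect on the other eight subscales. Holm never gives less power than Bonferroni and gives more if other subscales are also rejected, but the article states nothing that would support counting on that gain. All power figures are before any allowance for clustering of residents in wards and settings.

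**What to change.** Settle the rule before data are analysed.

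- **Preferred, because it fits the multidimensional research question:** keep all nine subscales and control the familywise error, either with Holm or with one joint test of the nine followed by adjusted subscale tests. Restate the sample size section to say that, with 70 per group and an effect of 0.50, power for a given subscale at the Bonferroni level is about 56% before clustering, and not 80%. If a joint test is chosen, give its power separately, with the assumed effects and correlations.
- **Alternative:** name one subscale as primary at two-sided 0.05, with about 84% power at 70 per group before clustering, and treat the other eight as secondary.

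Either way, say which subscale or test the effect size of 0.50 refers to. The cost is a change of wording and, under the preferred option, a less favourable power statement. No new data and no extra residents are needed. The 268 in the working shows what 80% per subscale at the Bonferroni level would require; it is not a proposal to enlarge the study.
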